# Study protocol: a pilot randomized controlled trial to evaluate the acceptability and feasibility of a counseling intervention, delivered by nurses, for those who have attempted self-poisoning in Sri Lanka

**DOI:** 10.1186/s40814-018-0341-1

**Published:** 2018-09-24

**Keywords:** Non-fatal self-poisoning, Counseling, Nursing

## Abstract

**Background:**

Deliberate self-harm in the form of non-fatal self-poisoning is a major public health problem in Sri Lanka. Previous work suggests that many nurses in Sri Lanka—particularly those who work in primary care in the medical treatment of persons who attempt self-poisoning—already approach their role in a holistic fashion and consider “advising” or “counseling” patients after self-poisoning to be a part of their nursing role. But there is no formal training given to such nurses at present nor has the efficacy or feasibility of such an intervention been assessed in Sri Lanka. The aims of this pilot study are to explore the potential efficacy, acceptability, and feasibility of carrying out a counseling intervention that could be delivered by nurses for persons who present to hospital for medical management of non-fatal self-poisoning.

**Methods/design:**

The study will be carried out at the Toxicology Unit of Teaching Hospital Peradeniya, Sri Lanka. A pilot randomized controlled trial will be carried out among participants admitted to Teaching Hospital Peradeniya for medical management of non-fatal self-poisoning. The primary objective of this study is to explore the acceptability and feasibility of a counseling intervention being delivered by nurses. The secondary objectives are to explore the efficacy of the intervention for the improvement of skills to cope with situations of acute emotional distress, and to reduce rates of anxiety, depression, and future repetition and suicidal ideation. A nurse’s experiences and attitudes regarding the acceptability and feasibility of implementing this intervention and participant experiences of the intervention and its effects will be explored via qualitative interviews and focus group discussions.

**Discussion:**

It is anticipated that the findings of this pilot study will help determine and assess the acceptability and feasibility of this counseling intervention, as well as indicate the more useful aspects of this intervention in order to develop it for further exploration in a larger trial.

**Trial registration:**

SLCTR/2017/008 Registered on 21st March 2017

## Background

Non-fatal self-poisoning is a major health problem in Sri Lanka [1]. Rates of hospitalization due to self-poisoning in Sri Lanka have increased in recent years; from 328 per 100,000 in 2004 to 463 per 100,000 in 2010 for males and from 270 to 421 per 100,000 with respect to females [2]. Recent studies indicate that there is a rise in medicinal overdoses in both urban and rural areas [3, 4]. Rates of self-poisoning are also high in Sri Lanka, Bangladesh, and India when compared with other South Asian low and middle-income countries (LMIC) [5].

Many terms—such as deliberate self-harm (DSH), attempted suicide, or attempted self-poisoning— are used to describe the behavior of those who deliberately ingest a poison or overdose a medication. For the purpose of this study, we use the term non-fatal self-poisoning, defined as deliberate ingestion of a toxic substance or ingestion of a medication in excess of its prescribed dosage.

Non-fatal self-poisoning in Sri Lanka appears to be associated with a combination of socio-demographic, cultural, and psychological factors [6]. The interpersonal conflict appears to be a common factor immediately preceding the act of non-fatal self-poisoning for both males and females, and the act occurs usually with only a small period of premeditation [7, 8]. Marecek et al., in their examination of self-poisoning by females in Sri Lanka, report that the act of self-poisoning is often associated with an interpersonal dispute, most often related to issues regarding the girl’s comportment and heterosexual relations [8]. Other studies describe a mixture of motivations associated with the act of self-poisoning, including a desire to die, a desire to escape, and difficulty tolerating distressing emotion associated with interpersonal conflict [7]. Factors such as physical, sexual, or psychological abuse and living in economically or psychologically stressful circumstances are also likely to contribute towards this behavior at times of crisis [9]. Particularly among older persons, psychiatric morbidity such as depression and alcohol use disorder in males is also likely to contribute [10, 11]. Lower socioeconomic status, unemployment, and lower levels of education have also been associated with self-poisoning [6, 12]. Stressful life events such as failed harvest, harassment at school, failed examination, and financial stressors are reported associated factors [9, 13].

### Psychological interventions for minimization of non-fatal self-poisoning

Internationally, many different types of psychological interventions have been explored to minimize this issue with varying results. Some interventions have been directed towards all patients presenting with non-fatal self-poisoning. Certain interventions have targeted specific subgroups—such as those suffering from depression or borderline personality disorder, specific ethnic groups, adolescents, or females and youth [14–17]. These include interventions based on cognitive behavior therapy, problem-solving therapy, family interventions, interpersonal therapy, and other innovative methods such as follow-up contact by telephone and postcards and short message services (SMS) [17–25].

However, studies reporting on interventions for DSH in non-western countries are scarce [24]. A study from Pakistan has reported that a culturally adapted, manual-assisted problem-solving therapy (C-MAP) was effective in reducing suicidal ideation and in improving quality of life and coping skills following self-harm [26]. This was a manual-assisted intervention, adapted from a self-help guide based on the principles of cognitive behavior therapy (CBT), and delivered by qualified psychologists.

Published interventional research for prevention of non-fatal self-poisoning in the Sri Lankan context is limited. One study conducted among young people in an urban population in Sri Lanka suggested that problem-solving counseling may be an effective and culturally acceptable therapeutic tool in the secondary prevention of suicides, which improved coping skills in the target group [27]. Another pilot has suggested that vendor-based sales restriction in regions with high rates of self-poisoning has the potential to reduce access to pesticides for self-poisoning in the Sri Lankan context [28]. However, there are only a few published data available regarding interventions for prevention of non-fatal self-poisoning in rural Sri Lanka, despite the widespread nature of the problem. Therefore, exploring interventions that are acceptable and feasible to carry out in a Sri Lankan social and cultural context is of importance.

### Nurses in mental health and counseling

Previous studies have shown that nurses indeed do engage in counseling of patients informally and without specific training in different community environments [29, 30]. A survey conducted by the World Health Organization (WHO) and the International Council of Nursing about nurses in mental health confirms that nurses are the central providers of most mental health services in many LMICs, but often with inadequate levels of training [31, 32]. Studies from Sri Lanka have shown that nurses also engage in providing mental health services in different communities. A recent study about nurses’ role in caring for and supporting women experiencing intimate partner violence in Sri Lanka has reported that nurses provide various kinds of support, including psychological support and advice to abused women [33]. Another study has shown that rural nurses who care for patients following non-fatal self-poisoning in rural Sri Lankan communities have a high level of first-hand knowledge of the patient’s life stressors and show understanding of how these interconnected and contributed as direct and indirect risk factors for self-poisoning [13].

Given the increasing rates of hospital admissions for non-fatal self-poisoning in Sri Lanka and the association with triggers such as interpersonal conflict, it is well worth exploring whether similar psychological interventions would be efficacious in improving coping skills. Such a psychological intervention would need to be adapted to the local culture and sustainable in the long term; while the field of mental health has developed greatly in Sri Lanka in recent years, an interventional therapy that requires large input from psychologists or even psychiatrists for its delivery is unlikely to be sustainable in the long-term, given how widespread the phenomena of self-poisoning in Sri Lanka is at present, combined with the current socio-economic constraints and limitations in trained resource personnel.

Thus, the primary objective of this study is to explore the acceptability and feasibility of a counseling intervention being delivered by nurses. The secondary objective is to explore the potential efficacy of the intervention for the improvement of skills to cope with situations of acute emotional distress and to reduce rates of anxiety, depression, and future repetition and suicidal ideation. It is anticipated that the findings of this pilot study will help determine and assess the acceptability and feasibility of this counseling intervention, as well as indicate the more useful aspects of this intervention in order to develop it for further exploration in a larger trial. It will also inform other aspects of a future trial, such as the sample size, indicate the level of loss to follow-up, and help assess treatment as usual.

## Methods/design

This will be a pilot randomized controlled trial (RCT) to evaluate and explore the efficacy of a counseling intervention delivered by nurses for persons who have been admitted to hospital for medical management of non-fatal self-poisoning (Fig. 1).

**Fig. 1 Fig1:**
[figure not shown]
Study flow chart

Primary outcomes will be assessment of feasibility and acceptability of the counseling intervention delivered by nurses. Acceptability and feasibility of this intervention, as experienced by the nurses who deliver the intervention and the participants who receive the intervention, will be assessed qualitatively. The secondary outcome is to explore the potential efficacy of the intervention for the improvement of skills to cope with situations of acute emotional distress and to reduce the rates of anxiety, depression, and future repetition and suicidal ideation.

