#### Delivery of the intervention

The intervention will be delivered by one or two designated trained nursing officers who have an interest in this new role and are willing to deliver the intervention. The details of the nurses training have been described previously.

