### Phase 2—Qualitative study

The qualitative component of this study complements the quantitative component of the study. Using qualitative methods, we will explore the feasibility and acceptability of the newly introduced intervention in a large tertiary care hospital setting, from the point of the nurses as well as those who receive the intervention, and will explore a range of perspectives.

We will conduct qualitative in-depth interviews with the participants during the hospital stay (pre-intervention) and follow-up (post-intervention). This is a central part of the qualitative study as we consider the experiences of nurses who deliver the intervention and participants to be crucial to evaluate the acceptability and feasibility of the counseling intervention. Further, we recognized that the screening instruments using in the quantitative study may not fully capture the complex interplay of factors that may contribute towards the act of self-poisoning. The qualitative component of the study will help explore the social and cultural aspects related to non-fatal self-poisoning which could be effective to develop future interventions to reduce non-fatal self-poisoning in Sri Lanka. These interviews will be also conducted with a view of the triangulation of qualitative and quantitative data.

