### Interviews with nurses who deliver the intervention

In-depth interviews will be conducted with the two designated trained nurses who voluntarily engaged to delivered the intervention, soon after the completion of the intervention period (of the RCT), to explore feasibility and acceptability of the intervention, as perceived by the nursing officers. The interviews will allow them to share stories and challenges broadly in an open approach. The nurses’ overall experiences regarding their new role of counseling persons who have attempted self-poisoning will be explored. This will include their perceptions of the experiences of delivering the intervention—whether they thought the training was adequate—use of the manual, what skills they think are needed for being an effective counselor, impact of age or service experiences of nurses on delivering the intervention, and challenges they faced and their suggestions for further improving the process. This will be conducted allowing the maintenance of an open approach so that the participants can bring in their own perspectives.

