#### Interviews with study participants

Similarly, qualitative interviews will be conducted among the study participants who received counseling from the nurses, as well as those who did not receive the counseling intervention, during the hospital stay and at 6 months follow-up. Exploring perceptions, experiences, and attitudes of the participants about the counseling they received from the nurses is the key in order to explore the acceptability of the intervention from the recipients’ point of view. We will also explore their attitudes and perception towards the counseling intervention they received and whether they found it helpful or unhelpful with regards to coping with situations of emotional distress. These interviews will also explore the characteristics of nurses as counselors that participants identify as supportive or unsupportive and to see whether this can be taken into consideration to the further improvement of the intervention.

We will also explore participant experiences after the act; the factors or reasons for the act as perceived by the participants and their family reaction towards the act. Further interviews will also be used to explore the way participants perceive how they cope with situations of acute emotional distress pre- and post-intervention.

The interviews will be semi-structured, guided with a theme list to cover all relevant issues during the interview, and will be conducted in Sinhala in a culturally sensitive manner. It is anticipated that the interviews will encourage participants to share sensitive issues and stories relating to the self-poisoning incident.

Participants will be selected following maximum variation sampling strategy technique [44], representing different age groups, employment groups, ethnic groups, and rural/ urban origin for the interviews, and interviews will be conducted until data saturates.

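### The primary feasibility and acceptability outcomes are fixed as qualitative only, and recipients' views of the session are first collected at return visits 6 months or more later

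*Protocol article*

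**What the plan says.** All references are to the protocol article.

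- **Primary outcome** (Methods/design, below Fig. 1): "Primary outcomes will be assessment of feasibility and acceptability of the counseling intervention delivered by nurses". The next sentence says how: these outcomes, "as experienced by the nurses who deliver the intervention and the participants who receive the intervention, will be assessed qualitatively".
- **Timing of participant interviews.** The Phase 2—Qualitative study section places them "during the hospital stay (pre-intervention) and follow-up (post-intervention"), and the Limitations section labels the hospital interview pre-intervention as well. The section on interviews with study participants gives "during the hospital stay and at 6 months follow-up". The follow-up section puts the acceptability interviews under a heading that covers both 6 months and 1 year, and holds the assessments at the recruiting hospital.
- **Nurses.** The session is delivered by "one or two designated trained nursing officers who have an interest in this new role and are willing to deliver the intervention". The section on nurse interviews has two: "In-depth interviews will be conducted with the two designated trained nurses who voluntarily engaged to delivered the intervention".
- **Session window** (Description and delivery of the trial intervention): one session of about 30 minutes, in hospital, within a week of the attempt and before discharge.
- **Retention.** The end of the Background says of the pilot: "It will also inform other aspects of a future trial, such as the sample size, indicate the level of loss to follow-up". The section on non-attenders defines a person as lost after two unanswered telephone calls and an unanswered written reminder. The sample-size section allows for 50% drop-out.

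**The concern.** The trial exists to prepare a larger one, and its main question is whether nurses can deliver this session and whether patients accept it. Three features of the stated method weaken the answer.

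First, recipients are asked about a half-hour conversation only after six months or more, and only if they come back to the hospital. Those who found it unhelpful may be less willing to return. The authors themselves rejected a multi-session intervention partly because they expected high attrition if participants had to come back after discharge.

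Second, someone allocated to counseling who declines it, or goes home before it can be given, is direct evidence on feasibility. The primary outcome is defined through nurses who deliver and participants who receive, so this person falls outside it.

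Third, the Discussion expects time constraints and negative attitudes among nurses as barriers. One or two interested volunteers describing their own delivery are poorly placed to show the second of these.

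At stake is whether the larger trial is planned on a view of acceptability that is more favorable than the full intervention arm would give, and on a feasibility outcome with no number in it.

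**Working it through.** **1. When recipients can first comment on the session**

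| Time point | What happens | Can a recipient comment on the session? |
|---|---|---|
| Hospital stay, before the session | Qualitative interview and scales | No, it has not yet happened |
| Hospital stay, after the session, before discharge | No participant assessment named | No |
| 6 months, return visit | Qualitative interview and scales | Yes, if the person attends |
| 1 year, return visit | Scales; qualitative interview according to the follow-up section only | Yes, if the person attends |

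The first opportunity is therefore at 6 months. The two sections that differ on a 1-year interview do not alter that.

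**2. Who can be heard**

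Interviewees are chosen by maximum variation on age, employment, ethnic group and rural or urban origin, until saturation. Neither attendance at follow-up nor uptake of the session is among the listed dimensions, so the sampling scheme does not correct for either.

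**3. The plan's own figure**

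Inputs from the sample-size section: difference 4.7, SD 4.49, two-sided 0.05, power 80%, drop-out allowance 50%.

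- n per group = 2 × (1.960 + 0.842)² × (4.49/4.7)² = 2 × 7.85 × 0.913 = 14.3, rounded up to 15. An exact t-test calculation gives 15.35; power at 15 per group is 79.0%.
- With drop-out: 15 / (1 − 0.5) = 30 per group.

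Both figures reproduce the document's 15 and 30. They concern the PHQ-9, which is a secondary measure. No figure is attached to the primary outcome.

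**4. What precision numeric feasibility measures would have**

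Half-width = 1.96 × √(p(1 − p)/n), with the Wilson 95% interval alongside. The 80% delivery rate is an assumption. The 50% retention is the document's drop-out allowance, used here only as an example. The planned 150 is read as the total (75 per arm); the text does not make this clear, so the other reading is shown too.

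| Measure | n | Simple half-width | Wilson 95% interval |
|---|---|---|---|
| Delivery 80%, counseling arm | 75 | 1.96 × √(0.16/75) = 9.1 points | 69.6% to 87.5% |
| Retention 50%, both arms | 150 | 1.96 × √(0.25/150) = 8.0 points | 42.1% to 57.9% |
| Retention 50%, one arm | 75 | 1.96 × √(0.25/75) = 11.3 points | 39.6% to 61.7% (38 of 75) |
| Delivery 80%, if 150 per arm | 150 | 1.96 × √(0.16/150) = 6.4 points | 72.9% to 85.6% |
| Retention 50%, if 300 in all | 300 | 1.96 × √(0.25/300) = 5.7 points | 44.4% to 55.6% |

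The number of eligible patients is not given, so no precision can be stated for the consent proportion.

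**The case against.** Much can be said for the plan, and several stronger readings fail.

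- **Qualitative work is a legitimate way to study acceptability in a pilot.** This stands. The weakness lies in using it alone for feasibility, and in when and from whom it is collected.
- **A reader might infer that the trial will yield no retention rate.** It will: loss to follow-up is a stated product of the pilot and has a working definition. It is simply not part of the primary outcome. The Background promises no recruitment or delivery figure, so no promise is broken there.
- **A reader might take the 50% as a forecast.** It is a sample-size allowance. The plan also provides telephone and letter reminders, travel reimbursement and repeat contact.
- **A reader might infer that the plan could never conclude that the intervention is not feasible.** The interviews ask nurses about challenges and adequacy of training, and ask participants whether the counseling was helpful or unhelpful and which nurse characteristics were unsupportive. The researcher stays in contact with the nurses about difficulties. An unfavorable conclusion is possible. Focus groups are also mentioned in the abstract and under Data management, though without their composition.
- **A reader might want the bias as a percentage.** The output is themes from a purposive sample, not an acceptability rate, so such a figure would not describe anything that the trial reports.
- **Those who missed the session might be covered,** because interviews include participants "as well as those who did not receive the counseling intervention, during the hospital stay and at 6 months follow-up". This most naturally means the control arm, and the primary outcome still names only those who receive the intervention.
- **This is a condensed article,** and screening logs, delivery counts and progression rules may stand in the full protocol. That is fair: the absence of a progression threshold is not held against it. What remains is a method that the article itself states for its primary outcome.

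**Conclusion.** The point holds as a limited weakness in a stated method. The primary outcome is qualitative only. It draws on one or two volunteer nurses and on recipients who return at 6 months or later. Participants allocated to counseling who do not receive it are not named as informants.

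The likely direction of bias is towards acceptable, on the assumption that dissatisfied participants return less often and that interested nurses are more favorable than their colleagues. Its size is unknown, and the selection part would be zero if returners and non-returners held the same views. Delay adds recall error whatever the attendance.

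The design can already supply useful numbers: about ±9 points for delivery (80% in 75) and ±8 points for retention (50% in 150), if 150 is the total. The pilot is not invalid as it stands, but these are inexpensive improvements to its main result.

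**What to change.** 1. Add a brief acceptability rating with one or two open questions for intervention participants, completed after the session and before discharge. Existing research staff should give it, not the nurse who counseled. Record who declined the session and who left before it could be held.
2. Keep the qualitative work for acceptability. Add to the primary feasibility outcome, each with a 95% confidence interval:
   - the proportion consenting among those eligible;
   - the proportion receiving the session before discharge and within 1 week of the attempt (the protocol's own window) among those allocated to counseling;
   - the proportion retained at 6 and at 12 months, by arm.

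In the same edit, state whether 150 is the total or per arm, and reconcile the sections that differ on a 1-year interview and on the number of nurses.

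The cost is one short form per intervention participant, a small added burden before discharge, and tabulation of enrollment, delivery and follow-up records. Randomization, treatment and sample size are unchanged.
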